### Sample Size Calculation

In this study, per ward 40 patients will be included per time point. This number is based on earlier studies evaluating physical behavior with the behavioral mapping method [39]. Patients will be included on 4 wards, leading to a total study population of 160 patients. To check if this number is adequate for powered effectiveness analyses, a sample size calculation was performed. For the sample size calculation, unpublished observation data from the UMC Utrecht in 2016 were used, in which 80 patients across the hospital were observed according to the behavioral mapping method. These data demonstrated that patients spent 56.01% of the time lying, with an SD of 32.53. On the basis of an earlier study evaluating the implementation of a multidimensional intervention to improve patients’ physical behavior, a decrease of 15% in the time spent in bed is expected to be feasible [18]. According to the sample size calculation, including a power of 80% and a P value of .05, a sample size of 74 patients would be needed. This confirms that the proposed sample size of 160 patients is more than adequate to evaluate the effectiveness of Hospital in Motion.

### Process Evaluation

Process evaluations are advised to monitor implementation processes of complex interventions and to evaluate factors of influence on the implementation. In this study, the framework of the medical research council guideline 2008 is followed to guide the process evaluation [40]. The 3 key functions of this framework include implementation, mechanisms of impact, and context. Implementation contains the goals and interventions that have been delivered by the project, including the adaptations, dose and reach, and how this delivery is achieved. The mechanisms of impact include the response (of caregivers and patients) to the interventions, the mediators, and all unexpected pathways and consequences. Context includes all other factors that may affect the implementation, interventions, and outcomes, such as barriers (eg, openness to changes, motivation, workload, and money) and facilitators [40]. For the process evaluation of the Hospital in Motion study on the different wards, a caregivers’ survey, a patient survey, and semistructured interviews with patients and caregivers are developed, which contain items of the 3 key functions of a process evaluation. The caregivers’ survey and the patient survey will be conducted before and after the implementation period. The semistructured interviews will be conducted at the end of the implementation period (Figure 3).

For the caregivers’ survey, questions are formulated focusing on the willingness to change and motivation of the caregivers to help improve patients’ physical behavior. In addition, questions are included to investigate the current state of the 6 topics of the action plan. The scoring of the questions is based on the visual analog scale; a score between 0% and 100% agreement can be given per question. The survey will be sent to all caregivers of the included wards before and after the implementation period.

For the patient survey, the level of encouragement patients perceived from care providers and the environment to be physically active in the past 2 days will be investigated using 6 statements with a 5-point scale. This patient survey will be performed before and after the implementation period. After the implementation, the survey will be supplemented with questions to investigate the success of the implementation of the action plans per ward.

**Figure 3 figure3:**
[figure not shown]
Timeline of process evaluation.

Semistructured interviews with patients and caregivers: After the implementation, semistructured interviews with both patients and caregivers will be undertaken. The interviews will be guided with a topic list based on the 3 key functions of process evaluation as described before [40].

### Statistical Analysis

All statistical analyses will be conducted using IBM SPSS statistics software 25. All outcome variables will be tested on normality with the Kolmogorov-Smirnov test. Patients’ characteristics will be described using descriptive statistics and tested with the Chi-square test, Mann Whitney test, or independent samples t test. Physical behavior is defined as the percentages of the total observed time that a patient spent lying, sitting, and moving. For both the primary outcome (the percentage of time spent lying) and the secondary outcomes (percentage of time sitting and moving), the changes in percentages after implementation will be analyzed. In addition, between-group analyses will be performed per ward. The differences between pre- and postmeasurements will be analyzed with an analysis of covariance, whereby the covariate(s) include baseline variables that may differ between pre- and postmeasurements. If data are not normally distributed, log transformation will be executed before testing.

The process evaluation will be based on the caregivers’ survey, patient survey, and semistructured interviews. Categorical data will be analyzed using Chi-square test and continuous data by using the Mann Whitney test or independent sample t test. To correct for multiple testing, a post hoc multiple comparison test will be performed. The semistructured interviews will be audio recorded and transcribed. Data analysis will follow 3 steps: coding, categorizing, and selecting themes, which will be performed in NVivo 11.

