Nevertheless, patients are reflexively put into pajamas, transferred into bed [15], and spend less than 6% of the day being active [2-4,9]. Lack of knowledge and time is often mentioned by caregivers as a barrier to promote physical activity [16,17]. This lack of time results in nurses prioritizing their medical tasks above assisting with patient mobilization and stimulating physical activity in patients with the ability to perform their own ADL tasks [16,17]. Studies targeting sedentary behavior during hospitalization have shown that physical activity is a modifiable factor that can prevent in-hospital functional decline [14,18-20]. These studies mostly focused on single interventions, whereas sedentary behavior is deeply rooted in the hospital culture. A multidimensional project focusing on environment, caregivers, and patients using multiple interventions may possibly be even more effective [21]. Even so, literature suggests that a comprehensive and flexible framework may help create sustainable interventions, leading to significant changes in clinical practice [22]. However, projects or studies to improve physical behavior focusing on the whole system, integrating physical activity in all levels of daily hospital care, are not common. Moreover, these studies focused mainly on elderly, whereas low mobility is of all ages [19,22]. Therefore, Hospital in Motion, a multidimensional project to improve patients’ physical behavior during hospitalization, has been developed.

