#### Primary Outcome

Physical behavior will be measured with the behavioral mapping method [30] and will be assessed before and after the implementation period (Figure 1). Patients will be observed on a random weekday of their stay in a fixed order every 10 min for 1 min. During this minute, the patients’ location, body position, daily activity, and direct contact will be registered [30]. A maximum of 8 patients per ward per day can be observed, and observations take place from 9 am until 4 pm.

Physical behavior is defined as the percentage of the total observed time that a patient spent in a specific body position. A distinction will be made between lying, sitting (bedside or chair), and moving (standing, transferring, walking, and cycling). The primary outcome in this study is the percentage of time spent lying.

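### The rule to log-transform the percentage outcomes after a failed normality test is the wrong remedy: it is undefined at 0%, skews time lying further and leaves the percentage-point scale

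*Protocol article*

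**What the plan says.** The Statistical Analysis section of the Protocol article sets a two-step rule. First: "All outcome variables will be tested on normality with the Kolmogorov-Smirnov test". Then: "If data are not normally distributed, log transformation will be executed before testing". Pre and post measurements are compared by analysis of covariance, with further analyses per ward.

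The rule covers the percentages of time lying, sitting and moving. The Primary Outcome section defines them: "Physical behavior is defined as the percentage of the total observed time that a patient spent in a specific body position". Time lying is primary. The article gives no treatment of zeros and no alternative to the log for these three outcomes. The Mann-Whitney test is named only for patient characteristics and the process evaluation.

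The Sample Size Calculation section works on the untransformed scale. Earlier observations showed that "patients spent 56.01% of the time lying, with an SD of 32.53", and "a decrease of 15% in the time spent in bed is expected to be feasible".

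**The concern.** A log helps when data are positive and right-skewed. Time lying is a share bounded at both ends, with a mean near the middle and a very wide spread. A patient who is never seen lying scores 0%, which has no logarithm. Such patients are those in whom the project succeeded most fully, and there should be more of them after implementation if it works.

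The rule governs the primary analysis. If it fires, someone has to decide after seeing the data whether zeros are deleted or a constant is added, and the answer depends on that choice. The test also moves off the percentage-point scale on which the study was sized. Because the trigger is a significance test on each data set, the scale may differ between wards and between outcomes.

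**Working it through.** **Inputs from the article.** Mean 56.01 and SD 32.53 for time lying, decrease of 15, power 80%, P=.05 (Sample Size Calculation). One observation every 10 minutes from 9 am to 4 pm (Primary Outcome), so 7 × 6 = 42 per patient. Forty patients per ward and time point on four wards. The stated total of 160 can be read as 160 in all (80 per time point) or as 160 per time point (320 in all), so both are shown.

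**Assumptions.** The article gives no distribution. Three shapes were simulated: a beta-binomial matched to mean and SD (alpha 0.79, beta 0.62), a clipped normal, and a clipped uniform (mean 55.6, SD 31.5). The normality test is taken at the 0.05 level. Power figures use two-sample t tests and the beta-binomial, with a post mean of 41% and the same SD.

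**1. The plan's own figure.** n = 2 × (1.960 + 0.842)² × 32.53² / 15² = 73.8, rounded up to the stated 74. This is per time point, with 15 read as percentage points on the raw scale.

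**2. Does the rule fire for time lying?** A normal curve with these values would put P(Z < -56.01/32.53) = P(Z < -1.72) = 4.3% below 0 and P(Z > 43.99/32.53) = P(Z > 1.35) = 8.8% above 100, so the outcome cannot be close to normal. Rejection rates across the shapes:

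| n tested | Lilliefors-corrected | uncorrected |
|---|---|---|
| 40 | 24-50% | not tabulated |
| 80 | 51-85% | about 2% under two of the shapes |
| 160 | 95-100% | 21-69% |
| 320 | 100% | 95-100% |

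The article does not say which version applies.

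**3. Does the log improve the shape?** Skewness of time lying is about -0.1 to -0.2 raw, -1.4 to -1.7 after the log with zeros dropped, and -1.6 to -1.9 for log(x+1). The mean Kolmogorov-Smirnov distance at n=160 rises from 0.10-0.11 to 0.17-0.23.

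**4. Zeros.** The chance of 0% lying is about 1-8% per patient across the shapes, so at least one zero is expected in 35-97% of samples of 40 and 82-100% of samples of 160. Under the beta-binomial it is 3.2% pre and 9.5% post.

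**5. If zeros are dropped.** The remaining means are 56.01/(1 - 0.032) = 57.9 and 41.01/(1 - 0.095) = 45.3. The 15-point fall becomes about 12.6.

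**6. If a constant is added.** The post/pre ratio of geometric means is 0.49 with a constant of 0.1 and 0.66 with a constant of 5.

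**7. Power** (simulation error is a point or two):

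| per time point | raw | log, zeros dropped | log(x+1) |
|---|---|---|---|
| 80 | 0.82 | 0.63 | 0.80 |
| 160 | 0.98 | 0.90 | 0.97 |

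**8. Time moving.** The Background section says patients "spend less than 6% of the day being active". With a common 6% rate and no variation between patients, 0.94^42 = 7% of patients score zero. With an assumed SD of 8 points it is 36%. Corrected rejection rates are 96-100% already at n=40. Here the log does reduce skewness (from 2.06 to 0.22 with zeros dropped, at SD 8), but the zeros remain undefined.

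**The case against.** The strongest reply is that the harm depends on how zeros are handled, a detail that a journal article may leave to a fuller document. That stands in part. A reader might infer that the rule by itself biases the primary estimate towards no effect and costs power. The documents do not support this, because nowhere do they say that zeros are deleted. With log(x+1) power is nearly unchanged, and the ratios of 0.49 to 0.66 lie further from 1 than the ratio of the means, 41/56 = 0.73. But the choice of the log is fixed in the article, and that choice creates the zero problem, worsens the shape and leaves the scale of the sample size.

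Four further limits hold:

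- It is tempting to say that the rule is certain to fire. That fits time moving and pooled time lying under the corrected test. It does not fit single wards, nor the uncorrected test at n=160.
- It is tempting to say that the mean and SD prove there are patients at 0% and 100%. They do not: two equal clusters near 24% and 88% give about the same mean and SD with no zeros. The zero rates are model outputs.
- The article places the log before testing and also promises analysis of changes in percentages. Percentage-point changes might therefore still be reported beside a log-scale P value. Test and estimate would then address different quantities.
- The 6% for activity comes from literature on the whole day. The trial's moving category covers 9 am to 4 pm and includes standing and transferring, so its zero rate is uncertain.

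**Conclusion.** The point holds in this form: the article commits the primary outcome and two secondary outcomes to a transformation unsuited to bounded percentages, through a trigger that is very likely in pooled data and unpredictable per ward. The mismatch with the raw-scale sample size follows from the article's figures alone. The worse skewness of time lying holds for every shape tried, though those shapes are assumptions; for time moving the log may help the shape. The loss of about 2.4 points of effect (15.0 - 12.6) and of 8 to 19 points of power is conditional on dropping zeros and on the beta-binomial. If 160 per time point is the right reading, power stays at about 0.90 even then. With an added constant, the cost is an estimate that depends on an unstated number.

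**What to change.** Delete the normality-test and log rule for the percentages of time lying, sitting and moving. State in advance that all three are analysed by ANCOVA on the original percentage scale, pooled and per ward, with heteroscedasticity-robust or bootstrap 95% confidence intervals, and report the adjusted pre-post difference in percentage points. A fractional-logit model can be named as an optional sensitivity analysis. Other pre-specified models that respect the bounds would also be defensible; what matters is that the scale is not chosen by a test on the data. The cost is one paragraph of wording and slightly more analysis work, with no extra patients or data.

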## Results

This study is ongoing. The first participant was enrolled in October 2017 for the premeasurement. The postmeasurements are planned for the end of 2018. The first results are expected to be submitted for publication in autumn 2019.

## Discussion

Despite the evidence about the negative consequences of low levels of physical activity, patients still spend most of the day in bed, leading to unnecessary functional decline and new disabilities in ADL [2,3]. Previous studies demonstrated that increased amounts of physical activity during hospitalization may prevent this functional decline [41]. Furthermore, 3 recent studies reported the results of the implementation of a single intervention to improve physical mobility during hospital stays [14,20,42]. The first study implemented a mobility scale and demonstrated an improved level of physical functioning on a general medicine unit [14]. The second study implemented an enforced mobilization protocol in patients following gastrointestinal cancer surgery and found a reduced number of postoperative pulmonary complications [20]. The third study is a large-scale study in which the implementation of specific mobilization goals (mobilization within 24 hours, mobilization 3 times a day, and progressive and scaled mobility) showed a 10% increase in the frequency of mobilization out of bed [42]. However, to integrate physical activity in usual care, multidimensional approaches with multiple interventions focusing on the whole system are suggested to be more successful [16]. The Eat Walk Engage program of Mudge et al is a good example of a multidimensional approach using multiple interventions, which demonstrated a reduced LOS after the implementation [19]. However, it still remains unclear if physical activity is a modifiable factor during hospital stay.

The Hospital in Motion study has the strength that it contains multiple interventions tailored per ward, developed by a multidisciplinary project team. In addition, it is one of the first known large projects using a multidimensional approach, focusing on the physical environment, caregivers, and patients, instead of only 1 element, to improve physical behavior during hospitalization. Another strength of the Hospital in Motion study is the primary outcome of physical activity. As previous studies mostly included medical outcomes (eg, LOS, remissions, and mortality), levels of physical functioning or frequency of mobilization and the actual amount and change of physical activity have not been evaluated [14,19,20,42]. To get more information about patients’ physical behavior, it is important to assess and evaluate the physical activity levels of patients during hospitalization. For this purpose, the behavioral mapping method is used. This method provides insight into the actual activity level of patients during an average hospital day and also assesses environmental factors such as the people in direct contact with the patient and the patients’ daily activity. This enables detailed evaluation of inpatient physical behavior and differences per ward.

Diverse factors could influence the success of the implementation of Hospital in Motion. The action plan is a multidimensional package of interventions aimed to improve physical behavior. It contains multiple interventions aimed to incorporate physical activity in usual care procedures, targeting the whole care system. This strength is a challenge at the same time. Many factors may affect the implementation process, such as the functioning of the project team, caregivers’ motivation and willingness to change, available time, and perceived workload. The appropriate study design has been discussed extensively within the research team because of the possible influence of confounding factors. As this study primarily aims to integrate physical activity in daily hospital care, more classic research designs (ie, randomized controlled trials) are less suitable. By following a step-by-step implementation process and by performing a process evaluation, the authors will provide useful insights into the changes in usual care and the successful and unsuccessful elements of the implementation process.

## Abbreviations

ADL: activities of daily living
AM-PAC: Activity Measure for Post-Acute Care
HAD: hospitalization-associated disability
LOS: length of stay
UMC Utrecht: University Medical Center Utrecht
